## Interventions

### Explanation for the choice of comparators

In this naturalistic study, the following potential comparators to NAT (treatment condition) evolve: (1) NAT clients awaiting treatment; (2) clients with clinically relevant symptoms who are either (2a) waiting for psychotherapy or (2b) receiving psychotherapy; (3) clients without symptoms waiting for follow-up; and (4) clients before vs. after NAT (individual trajectories of symptom development, Table 1).

**Table 1 Tab1:** Constellation of comparators

Treatment condition	Control condition	Limitation	Mitigation
[1] NAT	Awaiting NAT (RHS 13–36)	Reduced follow-up time points for those who wait for treatment; unknown N	-
[2] NAT	[2a] PT waiting [2b] PT receiving	Clients might still wait but may have started, or already finished PT; higher symptoms of the control group at baseline	Statistical control for the number of treatment sessions, use of the RDD
[3] NAT	Watchful waiting (RHS < 13)	Lower symptoms of the control group at baseline, low symptom levels generally	Evaluate number of clients who present with improving vs. deteriorating symptoms rather than
[4] After NAT	Before NAT	Within subject comparison; potential confounding factors	-

Note: RHS-15 = 15 item Refugee Health Screener with a sum score indicating symptom severity; PT = Psychotherapeutic sessions provided by a licensed Psychotherapist. Threshold to clinical relevance is suggested for ≥37. Watchful waiting is indicated for clients with ≤12 points

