### Intervention description

The NAT counselling intervention programme begins with an initial screening using the 15-item version of the Refugee Health Screener [123, 124]; to assess trauma exposure and symptom severity in adult refugees. Based on their RHS scores, participants are allocated into three groups: low (RHS ≤ 12; green), moderate (RHS 13–36; yellow) and high (RHS ≥ 37; red) severity of trauma reaction; high levels indicate clinical relevance (Table 2).

**Table 2 Tab2:** Allocation according to assessed trauma exposure and trauma reactions, taking into account safeguarding procedures

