## Assignment of interventions: allocation

Random allocation to treatment and control conditions is crucial in establishing causal inference. However, this approach is costly and raises ethical concerns when evidence-based treatment is existing and vulnerable populations are studied over extended periods. Therefore, the regression discontinuity design (RDD), introduced by Thistlethwaite and Campbell in the 1960s [141], serves as a powerful quasi-experimental alternative and has been applied in the field of counselling [142]. In brief, the RDD defines eligibility based on a *bandwidth* around a cutoff of a continuous variable that determines assignment. The premise underlying RDD is that participants near the cutoff are similar in all relevant respects except for treatment assignment, thus “as-if random” in this localized context. The *fuzzy* RDD also allows for deviation from the cutoff as criteria for single cases (systematic manipulation is however not allowed). With it, RDD provides an unbiased estimate of the local treatment effect, simulating a randomized controlled experiment for participants near the cutoff or within the bandwidth, respectively [141, 143–146].

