[3] To assess the effectiveness of NAT compared to the comparison groups (see Tables 1 and 4), we will combine the figures resulting from RDD with traditional approaches (GLM, clinical significance). In the RDD, we will calculate a local average treatment effect (LATE) of the intervention on primary (RHS-15) and secondary (LSNS, BRS, SWLS, SSS8) outcomes (see Table 1). To this end, we will firstly test whether the main criteria for a valid RDD are held. Using a graphical method (scatterplot), we will examine the relationship between the eligibility (RHS at baseline) and outcome (follow-up) variables. We expect the RHS score to be discontinuous at the cutoff values. In contrast, we do not expect to see discontinuities in relevant covariates at the cutoff, which would violate the assumptions of an RDD. Next, separate regression lines will be fit on both sides of a cutoff value using an ordinary least squares (OLS) regression as the starting point. Alternative functional forms will be tested with the goal of ensuring an unbiased estimation. The LATE will be computed directly as the difference between the regression lines at the cut-off (intercept). To test the statistical significance of the difference between the two conditions, we will use a *t*-statistic, dividing the treatment effect (difference between regression lines at cut-off) by the sum of the square of the standard errors of the comparison group (*SE*_*comparison*_) and the intervention group (*SE*_*interventio*n_). The calculated *t*-statistic will then be compared to a critical value from the *t*-distribution for the given degrees of freedom (*DF*). The degrees of freedom will be determined based on the number of the observations and the parameters estimated in the two separate regressions. In the most simple form, *DF = n*_*comparison*_
*+ n*_*intervention*_
*- 4*. The test will be two-sided. Moreover, we will run falsification tests and sensitivity analysis to ascertain the validity of the RDD [178], examine whether results are sensitive to the choice of bandwidth [144], run placebo tests on exogenous covariates and on the outcome at values other than the actual cutoffs [145]. Prespecified subgroup analyses will explore potential heterogeneity in treatment effects across different demographic and clinical characteristics. Adjusted analyses will account for potential confounding factors identified a priori.

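### Table 1, comparator [2]: the number of treatment sessions accrues after allocation and should not be a covariate in the main NAT versus psychotherapy contrast

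*Protocol article*

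**What the plan says.** Row [2] of Table 1 (protocol article, Explanation for the choice of comparators) sets NAT against clients waiting for psychotherapy (2a) or receiving it (2b). The stated limitation is: "Clients might still wait but may have started, or already finished PT; higher symptoms of the control group at baseline". The stated mitigation is: "Statistical control for the number of treatment sessions, use of the RDD". The table note defines the comparator in terms of sessions: "PT = Psychotherapeutic sessions provided by a licensed Psychotherapist".

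Allocation comes before any session. Under Intervention description: "Based on their RHS scores, participants are allocated into three groups", with 13–36 as the NAT group and the top group defined as "high (RHS ≥ 37; red) severity of trauma reaction". The allocation section rests the design on the premise that "participants near the cutoff are similar in all relevant respects except for treatment assignment", and says the fuzzy version "allows for deviation from the cutoff as criteria for single cases".

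Item [3] of the statistical methods defines the local average treatment effect as the gap between the two fitted lines at the cutoff. It restricts adjusted analyses to confounders identified beforehand and does not mention session count. Hypothesis 3 in Table 4 refers back to Table 1 for its control groups, so row [2] is part of the effectiveness plan.

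**The concern.** Whether a client in the referral group is still waiting, in therapy or finished at 6–9 months is a result of having been referred. It is not a nuisance that existed before allocation. Holding session count fixed therefore asks what the difference would be if both sides had attended equally often. That is a different question from what the programme's allocation rule achieves. Part of any advantage of the NAT pathway may lie in clients getting sessions that clients on a waiting list do not yet get, and that part would be adjusted away.

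The protocol also ties treatment received to symptom course. Under Criteria for discontinuing or modifying allocated interventions, a client whose trauma reactions deteriorate is re-assigned to the red group. Sessions attended can then carry information about how the client was doing, and conditioning on them can connect allocation with unmeasured prognosis. At stake is the interpretation of the NAT versus psychotherapy estimate for the primary outcome (RHS-15) and for the secondary outcomes analysed in the same way.

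**Working it through.** The plan states no figure on this point, so there is nothing to reproduce. The check is of timing and algebra.

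**Timing**
1. Baseline: the RHS score fixes the group (Intervention description; Implementation).
2. Afterwards: NAT or psychotherapy sessions accrue, or the client waits (Table 1, row [2]).
3. At 6–9 months: the face-to-face follow-up measures the outcome (Assessment (refugees)).

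Session count lies between allocation and outcome. It cannot be a confounder of baseline allocation.

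**What the basic cutoff model contains**

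The methods give DF = n(comparison) + n(intervention) − 4. Two lines with an intercept and a slope each use 2 × 2 = 4 parameters. The simplest planned model therefore has no session term.

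**What adding session count would do**

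Notation, all at the 36/37 cutoff and as NAT side minus referral side:
- τ = total jump in the outcome
- Δ = jump in mean session count
- a = effect of allocation not carried by sessions
- b = effect per session
- U = unmeasured prognosis, with effect g on the outcome
- λ = slope of U on session count within sides, at a given baseline score
- β = fitted session coefficient, taken as common to both sides

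If U does not jump at the cutoff, which is the design's own premise:
- τ = a + bΔ
- β = b + gλ
- adjusted jump = τ − βΔ = (a + bΔ) − (b + gλ)Δ = a − gλΔ

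Three cases follow:
- **No shared prognosis (gλ = 0).** The adjusted jump is a. The part bΔ is gone, and the estimand has changed.
- **Shared prognosis (gλ ≠ 0).** A further term −gλΔ appears. It is bias even for a, and its sign depends on gλ and Δ.
- **Equal mean sessions on both sides (Δ = 0).** The adjusted jump equals τ, and no harm is done.

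**Which sessions are counted**

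Table 1 does not say whether NAT sessions, psychotherapy sessions or both are meant, and the direction can turn on this. Let w be the share still waiting, m(N) the mean sessions on the NAT side and m(P) the mean among those who have started psychotherapy.
- **All sessions counted:** Δ = m(N) − (1 − w)m(P), which is positive if many are waiting.
- **Psychotherapy sessions only:** the NAT side has zero, so Δ = −(1 − w)m(P), which is negative once anyone has started.

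With helpful sessions and no shared prognosis (β negative), τ − βΔ moves against NAT in the first case when Δ is positive, and towards NAT in the second. None of b, gλ, w, m(N) or m(P) is given in the documents.

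**The case against.** The best case for the plan has four parts.

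**The cell pairs two limitations with two remedies.** In order, varying psychotherapy exposure goes with session control, and baseline imbalance goes with the regression discontinuity design. This is the natural reading, and it stands. A reader might infer that session control is meant to repair the baseline imbalance and fails at it, but the cell does not support that. The point is unaffected, because varying exposure is itself a consequence of allocation.

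**The methods text does not put session count in the cutoff model.** This also stands. A reader might infer that the regression discontinuity estimate as specified is already spoiled. The documents do not support that: the basic model has no session term, and the cell may intend the mixed model. As a covariate, session count would alter the contrast in either model.

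**Statistical control is shorthand in a condensed article.** It could mean a split by 2a and 2b, treatment received in a fuzzy analysis, or a secondary dose analysis. Part of this stands. However, the table commits to control for session count as the remedy for this contrast, and the article defines no dose or mediation estimand under which that would be right.

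**The mechanism is partly assumed.** The documents give no pattern of psychotherapy attendance or stopping, so it cannot be asserted that clients who do worse attend more. What they do show is re-assignment on deterioration, which makes dependence on symptom course possible but does not measure it.

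**Conclusion.** The concern holds in a limited form. Row [2] names a post-allocation variable, which is also the content of the treatments compared, as a statistical control. Used as a covariate in the NAT versus psychotherapy contrast, it would remove the effect carried by sessions. That conclusion assumes that mean session counts differ at the cutoff and that sessions affect the outcome. The added bias needs a further assumption: that sessions and outcome share unmeasured prognosis. The choice also sits badly with the plan's own definition of the treatment effect as the gap at the cutoff and with its limit on adjustment to confounders identified beforehand.

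No size or direction can be given. A reader might infer a spurious effect or a loss of a particular magnitude, but any such number would rest on assumed waiting shares, session effects and strength of confounding. A reader might also extend the point to every effectiveness analysis. Session count appears only in row [2], so the other three comparators are not touched. The point merits correction before analysis because the rule is stated and the repair is small.

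**What to change.** In Table 1, row [2], remove session count as a covariate from the main contrast and state the following:
- The contrast is estimated at the 36/37 cutoff by baseline allocation, with baseline covariates only.
- It is labelled NAT pathway versus psychotherapy-referral pathway, including waiting.
- Sessions attended and 2a/2b status are reported descriptively on each side of the cutoff.
- Departures from allocation are handled by the fuzzy design already planned.
- Any session-dose analysis is exploratory, with its own estimand, a statement of which sessions are counted, and its no-unmeasured-confounding assumption.

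One matching sentence in item [3] of the statistical methods would cover the mixed model as well. The cost is a table cell and a sentence, with no change to data collection. There is a small loss: the main contrast no longer isolates NAT against psychotherapy actually received, and the report should say so.

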### Implementation

To assign participants according to the RDD principles, we will use the RHS-15 (items 1–13) as eligibility criteria with two critical thresholds at 13 and 36 (see Fig. 4) as foreseen in the stepped-care model of the *NAT counselling intervention*. The RDD then assumes that the allocation to the conditions is nearly random within the determined bandwidth (RHS sum scores just above or below the cutoffs) and potential factors that would manipulate treatment effect vary randomly across participants in both groups. The *fuzzy* versus the *sharp* design version takes into account real-world implementation settings recognizing that participants with RHS scores in the yellow range need to be assigned to the red group, for instance, in cases of suicidal ideation or other negative psychological developments that requires treatment by clinical psychologist.

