#### Assessment (refugees)

Data collection from refugees begins with a face-to-face interview conducted by one of the NAT counsellors (see Sect. Intervention description) and continues with 10-minute monthly online assessments (Well-being Monitor). Approximately 6 to 9 months after the initial screening, refugees will be invited to a face-to-face follow-up interview.

At the start of the face-to-face baseline interview, we will ask for demographic information, screen for trauma related symptoms, and collect information on social and economic integration. The follow-up interview after 6–9 months will re-assess levels of psychological distress and integration.

The 15-item Refugee Health Screener [123] will be used to assess the severity of trauma related reactions. The RHS was adapted from validated instruments for depression, anxiety and PTSD to screen for trauma related reactions in refugee populations. Each item is rated on a scale from 0 (not applicable at all) to 4 (extremely) and a total score of items 1–13 indicates the severity of symptoms (0–52) and the intensity of treatment required. Items ask for instance for nightmares, loss of interest or other trauma related symptoms. Items 14 and 15 are taken into account in a qualitative way. The RHS was recently validated with refugees in the German context [124]. Kaltenbach et al. [124] found high sensitivity and good feasibility, reliability and validity for both the self-rating and interview versions. Strong psychometric properties of the RHS were also found in other studies in Germany [147, 148] and elsewhere [149, 150].

An adapted version of the Appetitive Aggression Scale [139] for refugees will be used to assess aggression. The AAS is a 15 item semi structured interview that measures appetitive aggression according to the extent of agreement to statements, on a scale ranging from 0 (disagree) to 4 (agree) for each item. A total sum score will be used to measure severity of aggression (max 60).

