Generalised linear mixed models (GLMM) with subgroups defined by the RDD will be used in addition and allow for integration of multiple follow-ups, if robust (*N*_min_ is sufficient to detect a small to moderate effect). Thus, to test the efficacy of NAT in comparison to our controls in regards to primary and secondary outcomes, we plan to use separate generalised linear mixed models (GLMMs) in R. To account for non-independence of measurements, we will include individuals as a random part of the models. To account for repeated measures, we will control the within-group variance for the effect of time, i.e. baseline and 3 and 6-month follow-ups, according to A Field, Z Field and J Miles [179]. To estimate the significance of the fixed terms, we plan to fit the models using maximum likelihood (ML), and compare models with and without each fixed term using likelihood-ratio tests [180]. In cases where the interaction term is significant, we will use post hoc Tukey tests using the R package emmeans [181] to assess which contrasts differ significantly. To correct for multiple comparisons controlling the false discovery rate, we will further adjust P-values accordingly [182].

Additionally, effect sizes will be estimated by calculating Cohen’s d [183] for within and between group differences following W Lenhard and A Lenhard [184]. Clinically significant change will be calculated using the reliable change index, following NS Jacobson, LJ Roberts, SB Berns and JB McGlinchey [185].

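### Table 1 row [3]: counting improving against deteriorating clients does not offset the baseline difference between NAT and watchful waiting, and favours NAT even when NAT has no effect

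*Protocol article*

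**What the plan says.** All references are to the protocol article.

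- **Explanation for the choice of comparators, Table 1 row [3].** The control is "Watchful waiting (RHS < 13"), and the admitted limitation is "Lower symptoms of the control group at baseline, low symptom levels generally". The mitigation is "Evaluate number of clients who present with improving vs. deteriorating symptoms rather than". The row does not define improving or deteriorating and does not mention the RDD. Row [2], which also faces a baseline difference, lists the RDD among its mitigations.
- **Intervention description.** The groups are "low (RHS ≤ 12; green), moderate (RHS 13–36; yellow) and high (RHS ≥ 37; red) severity of trauma reaction". NAT clients therefore start at 13–36.
- **Assessment (refugees).** On the RHS, "a total score of items 1–13 indicates the severity of symptoms (0–52) and the intensity of treatment required".
- **Implementation.** For the RDD, "we will use the RHS-15 (items 1–13) as eligibility criteria with two critical thresholds at 13 and 36".
- **Statistical methods, text and Table 4 on hypothesis 3.** The control group for symptom reduction is defined by pointing to Table 1. The analysis combines the RDD with conventional models and clinical significance. Further on, "Clinically significant change will be calculated using the reliable change index"; this sentence is not linked to any row of Table 1.

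**The concern.** The row recognises the right problem, but the remedy does not address it. A count of directions of change is fair between groups only if, without treatment, members of each group are about equally likely to move up or down. Here they are not, because group membership is itself decided by the baseline value of the score whose change is counted.

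Two mechanisms act in the same direction:

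1. **Regression to the mean.** Clients selected for low scores tend to score higher on retest. Clients selected for middling scores tend to move down, or stay level if the population mean lies near the middle of their range.
2. **The floor.** A green client can fall by at most 12 points (the baseline score) but can rise by 40 to 52. A yellow client can fall by 13 to 36 and rise by 16 to 39.

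Watchful waiting would then show fewer improvers and more deteriorators than NAT even if NAT did nothing. Because hypothesis 3 takes its control groups from Table 1, that contrast could be read as support for symptom reduction.

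**Working it through.** The protocol states no figure for this comparison, so there is none to reproduce. The check asks what the count shows when NAT has zero effect.

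**Inputs from the protocol.** Scale 0–52; green 0–12; yellow 13–36.

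**Assumed inputs (not in the protocol).** RHS mean/SD of 12/10, 16/11, 20/12 and 24/12; retest correlation r of 0.60, 0.75 and 0.90.

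**Step 1: hand check of regression to the mean.** With population mean m, the expected retest score at baseline x is m + r(x − m), with residual SD = SD·√(1 − r²). Take m = 20, SD = 12, r = 0.75, so the residual SD is 12 × √(1 − 0.5625) = 7.9.

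- Green client at 6: expected retest 20 + 0.75 × (−14) = 9.5. P(improve) = P(score below 5.5) = Φ(−4.0/7.9) ≈ 0.31. P(deteriorate) = P(score above 6.5) = Φ(3.0/7.9) ≈ 0.65.
- Yellow client at 24: expected retest 20 + 0.75 × 4 = 23. P(improve) = Φ(0.5/7.9) ≈ 0.53. P(deteriorate) = 1 − Φ(1.5/7.9) ≈ 0.42.

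**Step 2: simulation, zero effect.** Two measurements share the same true score, are rounded and clipped to 0–52, and are split on baseline. Percent improving / deteriorating, counting any change:

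| Mean/SD | r | Green | Yellow |
|---|---|---|---|
| 12/10 | 0.60 | 29 / 57 | 63 / 33 |
| 12/10 | 0.90 | 31 / 45 | 53 / 38 |
| 16/11 | 0.60 | 26 / 63 | 58 / 38 |
| 16/11 | 0.90 | 31 / 49 | 51 / 41 |
| 20/12 | 0.60 | 23 / 68 | 53 / 43 |
| 20/12 | 0.90 | 30 / 52 | 49 / 44 |
| 24/12 | 0.60 | 20 / 74 | 49 / 47 |
| 24/12 | 0.90 | 29 / 56 | 46 / 46 |

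Improvement rates at r = 0.75 lie between those at 0.60 and 0.90. Over all 12 scenarios, 20–31% of green and 46–63% of yellow clients improve. With an assumed 100 clients per group, a two-sided 5% test of the improved share is significant in favour of NAT in 70% to nearly 100% of trials. Where a common shift of −5 or +5 points was added for everyone (means 12, 20 and 24; r = 0.60 and 0.90), the direction did not change.

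**Step 3: floor alone.** Change is symmetric around baseline with no regression to the mean; mean 20, SD 10–12, SD of change 5–9. Improvement is about 37–43% in green against 46–48% in yellow. The floor is thus the smaller part.

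**Step 4: stricter definitions.** Counting changes of 5 points or more (12 scenarios as in step 2), 8–13% of green and 20–44% of yellow clients improve. If improvement meant reliable change, the limit would be 1.96 × SD × √(2(1 − r)); with SD 11 and r = 0.90 that is 1.96 × 11 × √0.2 = 9.6 points, so scores 0–9 could not qualify. Across the 12 scenarios no green client could qualify in eight, and 19–30% could in the four with r = 0.90.

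**Step 5: near the cutoff.** Comparing 10–12 with 13–15 (mean 20, SD 12) under no effect gives 34–39% against 38–41% improving. Most of the imbalance disappears.

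**The case against.** The best case for the plan has four parts.

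- **The RDD at the lower cutoff is already planned.** This stands. The Implementation section sets a threshold at 13, and the statistical text regresses follow-up on baseline RHS on each side of a cutoff. A reader might infer that the effectiveness conclusion rests on the row [3] count. The documents do not support that: the RDD and mixed models carry hypothesis 3, row [3] is one of four potential comparators, and the Limitations ask for results to be read as a pattern. What remains is that row [3] offers a biased contrast as its own remedy, and the Limitations name neither regression to the mean nor the floor.
- **The cell is incomplete in the available text and no test is stated.** This is also true, and the break is not held against the plan. The missing words would name what the count replaces; the count itself is stated.
- **Green clients can improve.** A reader might infer that most have no room to do so. The documents do not support that, because anyone scoring 1–12 can fall, and in the simulations 76–85% of green clients score above 0. It would hold only if improvement meant reliable change or a better colour group, and row [3] says neither. The reliable change index is named elsewhere and not tied to this row.
- **Confining the contrast to the cutoff costs numbers.** With mean 20 and SD 11, about 17% of clients score 10–15, which is roughly 77–128 of the 450–750 expected (30–50% of 1,500), before dropout. This is a real cost, but the planned RDD already bears it.

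**Conclusion.** The point holds in this form: the row [3] count does not mitigate the baseline difference it is meant to address, and it favours NAT under a null effect, mainly through regression to the mean after selection on baseline RHS and partly through the floor at 0. The direction was the same in all 12 scenarios. The size is assumption-based, because the protocol gives no RHS mean, SD or retest correlation: a gap in the share improving of about 17 to 34 percentage points for any change (29 against 46 at the smallest, 29 against 63 at the largest), or roughly 5 to 9 points from the floor alone. It should be corrected, but it is a flaw in one comparator, not in the whole effectiveness analysis.

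**What to change.** In Table 1 row [3], replace the mitigation with the RDD at the 12/13 cutoff that the Implementation section and the statistical methods already plan, with baseline RHS as running variable and RHS at 6–9 months as outcome, in line with row [2]. Add one sentence to the methods for hypothesis 3: improving and deteriorating counts for the green group are reported descriptively only, not as a contrast with NAT and not as evidence for that hypothesis.

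This changes one table cell and one sentence and needs no new data. The downside is that the row [3] contrast becomes local to the cutoff and uses fewer clients.
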